### Measurement instruments

Table 2 provides an overview of the measurement instruments used in the study. The primary outcome measures are the scale of the Communication of Basic Needs (CBN) on the Functional Assessment of Communication Skills for Adults (FACS) [28, 29]. Communication recovery is an essential outcome when people with aphasia are in hospitals. Although professionals agree the outcome is important, there is no assessment tool in the Chinese language to evaluate the outcome. Therefore, the team translated the items of the CBN domain and its scoring scale to Chinese to measure the outcome of the AACT on communication effectiveness in a hospital setting.

**Table 2 Tab2:** Measurement instruments

Measurement instruments	Number of items	Score range	Measurement target
CBN subtest on the ASHA FACS	7	0–7	Functional communication skills for basic needs
ABC test	23	0–100	Language abilities, including speaking, listening, reading, and writing
10-min conversation	4	0–5	Communication efficiency in the in-patient setting
SADQH-10	10	0–3	Depression symptoms
SS-QOL	49	49–245	Stroke-specific health-related quality of life
Satisfaction questionnaire	11	1–5	Satisfaction intervention for communication improvement from both patients and their caregivers

The FACS measures functional communication skills of people with aphasia in four domains (social communication, communication of basic needs, reading/writing/number concepts, and daily planning) and in four qualitative dimensions (adequacy, appropriateness, promptness, and communication sharing). The 7-point scale measures the levels of assistance and prompting needed in each domain, and the 5-point scale measures the response in four dimensions. The inter-rater/intra-rater reliability for the CBN domain and the overall qualitative dimension are high. The concurrent validity between the Western Aphasia Battery and the Functional Independence Measure (FIM) is moderate [28].

An informal test of a 10-min conversation is used to measure participants’ functional communication efficiency in the in-patient setting pre- and post-intervention. Conversation analysis is a common procedure in regular aphasia assessment [30]. The 10-min conversation is evaluated using the 5-point scale of the four qualitative dimensions (adequacy, appropriateness, promptness, and communication sharing) in the FACS. The results of the 5-point scale allow the team to evaluate changes of the quality of conversation pre- and post-intervention. The participants are asked to talk about their daily lives and their medical services with the SLP in the conversation. The conversation will be video recorded and analyzed by the SLP conducting the assessments.

The secondary measures include the Chinese Standard Aphasia Battery (ABC), a standard test to diagnose aphasia and determine the type of aphasia for the Chinese-speaking population and widely used in clinical practice and research in local sites, to measure participants’ overall language performance [25]. The Chinese version of the 10-item Hospital version of the Stroke Aphasic Depression Questionnaire (SADQH-10) with adequate content validity and the test-retest reliability (> 0.80) is used for evaluating depressive symptoms in people with aphasia [31, 32]. The Chinese version of the Stroke-Specific Quality of Life Scale (SS-QOL) with high stability and validity is used for evaluating the stroke-specific health-related quality of life [33, 34].

For qualitative evaluations, the first author designed a 5-point scale questionnaire to evaluate the satisfaction of the interventions for this trial. The questionnaire includes four items for both control and experimental groups, three items for both groups’ caregivers, and two extra items for the experimental group and the caregivers. The questions were reviewed by the research team to ensure the readability and appropriates. The participants and their caregivers are asked to choose from 1 (very dissatisfied) to 5 (very satisfied) to evaluate the satisfaction for materials (common cards and AAC paper board) and communication behavior with caregivers and medical professionals after the intervention.

Figure 2 shows the schedule of each outcome measure. The CBN on the ASHA FACS, the ABC, a 10-min conversation, and SADQH-10 are completed pre- and post-intervention. The satisfaction questionnaire is completed after the intervention. The SS-QOL is completed after a 2-week follow-up for evaluating the quality of life after participants are discharged by the in-patient rehabilitation program. Additional file 1 is an overview of the Standard Protocol Items: Recommendations for Interventional Trials (SPIRIT) checklist.

**Fig. 2 Fig2:**
[figure not shown]
Trial schedule of enrollment intervention and assessment

### Sample size

No large RCTs have been conducted in the field of aphasia AACT in in-patient rehabilitation settings. Previous AAC studies used interventions not applicable to the current protocol. Therefore, we are unable to calculate the prior accurate sample size. We will use the CBN score in the FACS to investigate the possible effect. We consider a minimum improvement of 1 point on the 7-point scale in FACS is clinically significant. Given an expected standard deviation of 1 based on prior norm references [28, 35], the trial must include a total of 44 participants. Each group needs 22 participants to detect this difference with a significance level of 5 and a power of 90. After considering a dropout rate of 20%, the study aims to recruit 56 participants in total. We anticipate that this pilot study will provide information for more accurate sample size calculation in the future.

### Data analysis

Outcomes of interest will be analyzed on an intention-to-treat basis. Characteristics of the sample and the descriptive statistics will be reported. The primary analysis will be conducted without adjustment. The mixed model analysis will be used to analyze the continuous repeated-measure data because of its advantages of accommodating missing data and the flexibility in small samples and treating time. Data will be examined for differences between groups and over time. Post hoc tests will be performed to explore factors including age, sex, education, and initial stroke/aphasia severity, considered to affect the trial’s outcome. The data from conversation samples and the satisfaction survey will be suitably coded for qualitative responses to be categorized and examined.

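### The primary analysis is fixed as unadjusted and does not use pre-randomization CBN as a covariate or through a common baseline mean, so it gives up precision and saves nothing

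*Protocol article*

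**What the plan says.** The Data analysis section settles the question of covariates in one sentence: "The primary analysis will be conducted without adjustment". It names a mixed model for the repeated continuous measures and describes the comparison as "Data will be examined for differences between groups and over time". Demographic factors and initial severity appear only in post hoc tests.

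The Study design and procedure section places the baseline assessment before randomization. The Measurement instruments section has CBN scored before and after the intervention, so there are exactly two CBN values per participant.

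The Sample size section rests on CBN. "We consider a minimum improvement of 1 point on the 7-point scale in FACS is clinically significant"; the SD is introduced with "Given an expected standard deviation of 1 based on prior norm references"; and the result is "Each group needs 22 participants to detect this difference with a significance level of 5 and a power of 90". It does not say whether the SD of 1 is that of a single score or of a pre-post change, and it gives no pre-post correlation.

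**The concern.** The Objective section asks whether the combined-treatment arm improves more than the SLT-only arm. A baseline value of the same scale, taken before randomization and about two weeks before the post-treatment value, is usually among the strongest predictors of outcome. Conditioning on it cannot bias a randomized comparison and costs one degree of freedom. The plan's fixed sentence leaves it out as a covariate, and no common-baseline model is described in its place.

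Two things are at stake. The first is precision: the same 44 participants could give a narrower interval. The second is chance imbalance. With 22 per arm the standard error of the baseline difference is √(2/22) = 0.30 SD, so a gap above 0.3 SD in either direction arises by chance in about 32% of such trials. A post-score comparison carries part of that gap into the estimate, and so does a change score, in the opposite direction. Adjustment removes the predictable part.

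**Working it through.** **Inputs.** From the Sample size section: difference 1 point, SD 1, significance level 5%, power 90%, 22 per arm. From the Randomization and blinding section: 1:1 allocation. Assumed, because the document does not give it: the pre-post correlation ρ of CBN, taken over a range. Except in step 4, SD 1 is read as the SD of a single score.

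**Step 1: reproduce the stated figure.** n per arm = 2(1.960 + 1.282)² × 1²/1² = 21.01, rounded up to 22. A one-sided test would need 18, so the plan is two-sided. At 22 per arm, power is 91.3% by the normal approximation and 90.0% by the noncentral t with 42 df. Dropout: 22/0.8 = 27.5, hence 28 per arm and 56 in total. The stated size is therefore a plain, unadjusted comparison of two means, and it reproduces.

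**Step 2: SD of each candidate analysis.**
- Post-treatment score only: 1.
- Change, which is the group-by-time contrast of an unadjusted two-visit model: √(2(1 − ρ)).
- Post-treatment score adjusted for baseline: √(1 − ρ²).

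Power uses noncentrality 1/(SD × √(2/22)), with 42 df (41 when adjusted). Example at ρ = 0.3: the change SD is √1.4 = 1.183, noncentrality 2.80, power 78%. The adjusted SD is √0.91 = 0.954, noncentrality 3.48, power 92%.

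**Step 3: results, 22 per arm, two-sided 5%, t-based.**

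| ρ (assumed) | Post score, unadjusted | Change contrast, unadjusted | Baseline-adjusted |
|---|---|---|---|
| 0 | 90.0% | 63% | 89.9% |
| 0.2 | 90.0% | 73% | 91% |
| 0.3 | 90.0% | 78% | 92% |
| 0.4 | 90.0% | 84% | 94% |
| 0.5 | 90.0% | 90% | 96% |
| 0.6 | 90.0% | 95% | 98% |
| 0.7 | 90.0% | 99% | 99.5% |

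The ratio of change to adjusted variance is 2(1 − ρ)/(1 − ρ²) = 2/(1 + ρ): 1.54 at ρ = 0.3 and 1.18 at ρ = 0.7. In sample-size terms (normal approximation), 90% power needs 20, 16 and 11 per arm with adjustment at ρ = 0.3, 0.5 and 0.7, against 22 for the post score at any ρ and 30, 22 and 13 for the change contrast.

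**Step 4: the other reading of the SD.** If SD 1 is the SD of change, the change contrast has the stated power at every ρ (90.0% t-based, 91.3% normal). By the normal approximation, the unadjusted post-score comparison then has 97.5%, 91.3% and 72.9% at ρ = 0.3, 0.5 and 0.7, and the adjusted analysis has 98.4%, 96.9% and 94.9%. Under either reading, each unadjusted option falls below 90% somewhere in the range unless it happens to match the SD meant. The adjusted analysis does not fall materially below 90% under either reading.

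**The case against.** The strongest reply is that nothing here is invalid. Under randomization an unadjusted comparison is unbiased with correct type I error, the trial calls itself a pilot, and the exact model term may sit in an analysis plan that is not shown. All of that stands, and it is why this is an efficiency point.

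Three stronger readings are tempting, and the document does not support them.

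- *That the plan throws the baseline away.* With only two CBN values per participant, a repeated-measures mixed model most naturally takes the first one in as a response. The no-adjustment sentence most naturally refers to covariates such as demographics and severity, which the same paragraph leaves to post hoc work. What can be said is narrower: baseline CBN is not used as a covariate, and no common baseline mean is specified.
- *That lack of adjustment by itself brings power below 90%.* It does not. The stated 22 per arm is itself an unadjusted calculation and gives 90.0%. A shortfall needs a mismatch between the contrast and the SD: a change contrast with ρ below about 0.5 and a score SD of 1, or a post-score comparison with ρ above about 0.5 and a change SD of 1. The document fixes neither the SD type nor ρ.
- *That the test is a group main effect averaged over both visits.* That would halve the effect to 0.5 and give 55% power at ρ = 0.2 and 40% at ρ = 0.8. The phrase about groups and time is condensed article prose, and the Objective section asks about improvement. Nothing says that the averaged effect is the primary test.

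**Conclusion.** The point holds as a loss of precision. At ρ = 0.5, adjustment lifts power from 90% to 96%, or allows 16 per arm where 22 are planned. At ρ = 0.3 it gives 92%, against 90% for the post score and 78% for a change contrast. At ρ = 0 its cost is 0.1 percentage points (89.9% against 90.0%). These figures assume 22 completers per arm, a true difference of 1 point, a score SD of 1 and a roughly linear relation between baseline and outcome. Every ρ is an assumption.

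The plan is valid as it stands and its stated sample size reproduces, so this is a free improvement and not a condition for going ahead. The unclear meaning of the SD is a smaller, linked defect: until it is settled, no one can tell whether a given unadjusted contrast has the power claimed.

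**What to change.** In the Data analysis section, replace the no-adjustment sentence with wording such as: *The primary analysis will estimate the between-arm difference in post-intervention CBN, adjusted for baseline CBN, with a 95% confidence interval, using ANCOVA or a mixed model with a common baseline mean and arm-by-time as the primary contrast. The unadjusted result will be reported as a sensitivity analysis.* Choose one of the two models in advance. Adjustment for baseline ABC severity is optional.

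In the Sample size section, add whether the SD of 1 is that of a score or of a change, and the pre-post correlation assumed if one is used.

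The cost is two or three sentences and one degree of freedom. No new data are needed. The Trial status section reports fourteen participants randomized at publication, so the change could be made by formal amendment well before any unblinded analysis.

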## Discussion

This protocol describes a pragmatic pilot randomized controlled trial that can provide a valuable contribution to people with post-stroke moderate to severe aphasia in in-patient rehabilitation settings. The trial’s primary objective is to investigate the effectiveness of AACT combined with traditional SLT in communication/language recovery. To our knowledge, no RCTs have explored the combination of two treatment approaches for people with aphasia in in-patient rehabilitation settings.

This RCT will look at the feasibility of scaling the AACT up for larger trials and clinical implementation. Therefore, we aim to have a larger sample size compared to previous studies. While AACT has been developed several decades in developed countries, it is still relatively new for most developing countries, including China. Future studies may apply the results of the study to them if the trial is feasible. People with post-stroke aphasia commonly receive traditional SLT that aims to recover their verbal communication skills through behavior modification, cognitive therapy, and pragmatic therapies. However, many of them face immediate communication challenges when they are admitted to hospitals. Evidence suggests that people with aphasia have decreased quality of life, poorer health outcomes, and limited participation in medical encounters due to their communication and language disabilities [8]. These people are more likely to experience adverse medical events (e.g., medication errors) than those without a communication disability [8, 36]. AACT can be the solution to improve the situation. People with post-stroke aphasia can use AAC to support their communication effectiveness when spoken communication skills do not work [21].

Our trial trains people with aphasia to use a paper-based communication board with caregivers and healthcare providers in in-patient rehabilitation settings. It is easy to access and cost-effective, which is essential for all clinical settings. As an in-patient stay is often the first step on a long-term care continuum, AAC can maximize people’s communication skills with aphasia within desired life roles and prepare them and their families for life after the in-patient stay [8]. When the trial is completed, the results will also give us a better understanding of the AACT’s dual role in simultaneously driving inter-systemic reorganization with the potential to support language function while providing compensatory strategies during communication breakdowns in in-patient settings.

In our previous experience, AAC is often not prescribed in the early stages of recovery because patients with aphasia and their family members are worried that receiving AACT will impede language recovery [19]. It is a common AAC myth in clinical settings. However, recent evidence suggests that early AACT in in-patient settings may increase AAC acceptance and decrease the risk of not using language during the early recovery stage. Early AACT may also increase people with aphasia’s motivation to communicate in various situations and have better long-term participation outcomes. Therefore, they were more active when making their healthcare decisions, experiencing increased participation in life events, and discovering new social roles [19]. This evidence supports the purpose of the trial’s intention to investigate early AACT’s effectiveness in in-patient settings. The results of the trial will also contribute to the research evidence of AACT in Chinese-speaking people with aphasia.

A limitation of this study is that this protocol is not double-blind. However, the participants and the SLP will be blinded to treatment allocation. The study also cannot eliminate the confounding effects from the early-stage spontaneous recovery after stroke. The trial is designed to investigate the effectiveness of the current practice protocol in the local site. Therefore, the follow-up is short. Since the research evidence of the effectiveness of AACT in in-patient settings is limited, the trial’s results will also provide new insight into implementing AACT in actual clinical practice.

## Trial status

This trial is registered in the Chinese Clinical Trial Registry database (ChiCTR) as ChiCTR2000028870 on 5 January 2020, and the current protocol is the first version. The recruitment of the trial started on 20 January 2020, and delay the completion time until December 2022 as reported in the ChiCTR database due to the research site’s restriction of admitting patients because of COVID-19. Fourteen participants have been recruited and randomized into the trial until now.

## Data Availability

The datasets analyzed during the current study are available from the corresponding author on reasonable request.

## Abbreviations

AAC: Augmentative and alternative communication
ABC: Aphasia Battery of Chinese
ASHA: American Speech and Hearing Association
CBN: Communication of Basic Needs
CONSORT: Consolidated Standards of Reporting Trials
FACS: Functional Assessment of Communication Skills for Adult
MEC: Medical Ethics Committee
RCT: Randomized controlled trial
SADQH-10: 10-item Hospital version of the Stroke Aphasic Depression Questionnaire
SLP: Speech and language pathologist
SLT: Speech-language therapy
SPIRIT: Standard Protocol Items: Recommendations for Interventional Trials
SS-QOL: Stroke-Specific Quality of Life Scale
YY hospital: Yueyang Hospital of Integrated Traditional Chinese and Western Medicine Affiliated to Shanghai University of Traditional Chinese Medicine
